## 4. Conclusions

This study aims to test a preventive e-mental health offer for relatives of people with Parkinsonism. It will be apparent whether the target group accepts this offer and what suggestions and feedback are revealed in the evaluation. With the help of feedback, especially from the interviews, the psychosocial intervention will be further developed to ensure that the offer is oriented according to the needs of the relatives. After evaluating the pilot study, a modification of the intervention and the study design is planned, relying on the findings. Based on this, a multicenter randomized, controlled trial will be implemented.

## Figures and Tables

**Figure 1 brainsci-12-00442-f001:**
[figure not shown]
Schematic course of the study for each dyad.

**Table 1 brainsci-12-00442-t001:** Core outcome set and measurement instruments.

Measurements	Outcome	Baseline	Post Intervention	Follow-Up (6 Weeks)
**Patients**				
Sociodemografic data	Personal data	x		
Big-Five-Inventory 10 (BFI)	Personality	x		
PDQ-39	Health status regarding PD	x		
Beck’s Depression inventory (BDI-II)	Depression	x		
**Relatives**				
Sociodemografic data	Personal data	x		
Montreal Assessment (Moca) Blind 8.1	Cognition	x		
Parkinson’s disease caregiver burden questionnaire (PDCB)	Burden on family carergiver	x	x	x
Zarit Burden Interview (ZBI)	Burden on family carergiver	x		
Beck Depression inventory (BDI-II)	Depression	x	x	x
Health-related quality of life (EQ-5D)	Health-related quality of life	x	x	x
Coping Inventory for Dealing with Stressful Situations (CISS)	Coping strategies for stressful situations	x	x	x
Questionnaire on Health-Related Resources and Self-Management Skills (FERUS)	Health-related self-management strategies	x	x	x
Therapy Expectancy and Evaluation Questionnaire (PATHEV)	Therapy Expectancy	x	x	
Big-Five-Inventory 10 (BFI)	Personality	x		
Subjective Benefit (Credibility/Expectancy Questionnaire (CEQ))	Subjective Benefit		x	
Semi-structured Interview	Feasibility of the intervention		x	x

**Table 2 brainsci-12-00442-t002:** Feasibility analysis.

Outcome	Measurement Instruments	Operationalisation
Feasibility of the Intervention		
Acceptance	Interview	Willingness of the target group to participate
		Reasons for participation
		Evaluation of the digital intervention
Fit	Interview	Scope of the intervention
		Effort for the relatives
		Choice of timing
		Suggestions for optimization
		Overall assessment
Subjective Benefit	Interview	Particularly helpful aspects
		Psychosocial changes that the relatives notice about themselves
Evaluation of the intervention	Questionnaire (Filled in by the relative)	Questionnaires for the evaluation of each session
Feasibility of the intervention manual		
Adherence	Questionnaire (Filled in by Advisor)	Assess whether all intended aspects of the intervention have been discussed. A maximum of 14 points can be achieved
Feasibility of the study design		
Quality criteria	Expert panel	Quantiative: Validity, reliability, objectivity Qualitative: Transparency, intersubjectivity, range Drop-Out-Analysis

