## Abstract

Research on support for relatives of patients with Parkinsonism has mainly focused on caregivers, while preventive offers for non-caregiving relatives are lacking. Thus, the aim of this multicenter pilot study is to develop and assess the feasibility of a preventive psychosocial support program for relatives of patients with Parkinsonism. It specifically focuses on family members of patients who are in an early phase of the disease, are not currently caregiving, and have not yet developed distress symptoms. It includes a telemedicine-based, 6-week preventive psychological short intervention (PPSI). The main objective of this feasibility mixed-methods study is to specify the demand for an early, low-threshold, and low-cost short intervention and to collect feedback based on qualitative and quantitative data of *N* = 20 relatives. Secondary objectives are an evaluation of the effects of the intervention and an analysis of the study design. Future directions are to further develop the PPSI using these data. This study can serve as a basis for future randomized controlled studies on this intervention, which might fill an important gap in clinical supply.

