The intervention itself is solely aimed at the non-caregiving relatives and intends to strengthen resources, thereby fostering empowerment in the course of a progressive disease. Topics of the intervention, which follows a cognitive–behavioral therapy approach, are, on the one hand, the visualization and activation of relatives’ social network of relationships, and, on the other hand, specific exercises with relatives of people with Parkinsonism to empower dealing with stressful situations possibly arising in the future. The intervention is offered online and allows participation from home to facilitate implementation into relatives’ everyday life. The key question is, therefore, a threefold feasibility analysis:Feasibility of the intervention: the feasibility will be assessed via acceptability, fit and subjective benefit.Feasibility of the manual (adherence): it is to be assessed whether all planned aspects of the intervention have been discussed or if there are other topics that will be brought up by the relatives.Feasibility of the study design: investigating the feasibility of the study design means critically reflecting on the mixed-methods approach, the process of a baseline measurement with post and follow-up assessments, as well as the validity of the questionnaire selection and the structure of the interview guide. The data from questionnaires will be used for exploratory analyses.

Against this background, the primary aim of this multicenter pilot trial following a mixed-methods approach is to develop and assess the feasibility of a preventive psychological short intervention to relatives of patients with Parkinsonism at early stages. In addition, the secondary aims are to investigate the effects and manual adherence of the intervention.

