## 2. Methods and Study Design

### 2.1. Methods

This study will be conducted at two different locations in Germany, the Department of Neurology of the University Hospital in Marburg (study number: 175/20) and the Department of Medical Psychology/Neuropsychology and Gender Studies of the Faculty of Medicine and the University Hospital Cologne of the University of Cologne (study number: 21-1061). Ten patients and ten relatives will be included as dyads per site so that a total of 20 relatives and 20 patients with Parkinsonism will be included. Recruitment will take place separately at both sites. At the Marburg site, patients and their relatives will be recruited via an internal recruitment system of the Department of Neurology at the University Hospital that lists patients with Parkinsonism who are generally interested in participating in studies. In Cologne, recruitment will be ensured via lists of study participants from previous studies. Further, e-mail distribution lists of self-help groups will be used to increase the recruitment numbers.

Inclusion criteria for patients are: (1)Patients with a clinical diagnosis of Parkinsonism according to the Movement Disorder Society (MDS) criteria [2];(2)Patients aged ≥ 18 years;(3)Hoehn and Yahr stages I–II (OFF-state).

The exclusion criteria for the patients are:(1)Hoehn and Yahr stage ≥ III (OFF-state);(2)No care requirements and/or outpatient or inpatient care;(3)Suspected dementia according to physicians’ reports and (third-party) anamnesis.

Inclusion criteria for non-caregiving relatives are:(1)Partners of people diagnosed with Parkinsonism, living together in the same household;(2)Age ≥ 18 years;(3)Not involved in informal caregiving of the subject with Parkinsonism;(4)Willingness to use telemedicine, availability of a PC or tablet with stable internet connection;(5)No cognitive impairment (operationalized by the Montreal Cognitive Assessment [MoCA] [38], Blind Version ≥ 19; the MoCA Blind, which is suitable for online administration and therefore used here, is reduced to 22 items and converted back to 30 points maximum. A total of 19 points in the MoCA Blind version correspond to 26 points in the original MoCA “Full”);

Exclusion criteria for the relatives are: (1)Own caregiving requirement;(2)Severe depression (operationalized by the Beck’s Depression Inventory-II [BDI-II] ≥ 29 points) [39].

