#### 2.4.2. Feasibility Analysis of the Intervention

The qualitative data will provide a more detailed insight into the perspective of relatives of patients with Parkinsonism as potential future primary caregivers. Qualitative, semi-structured interviews will be conducted at two time points via an online consultation with relatives immediately after the intervention (t1) and 6 weeks post-intervention (t2). This part of the feasibility analysis is structured by the three outcome aspects of acceptance, fit, and subjective benefit with corresponding operationalizations and queried in the interviews. The interview guide contains questions on acceptance, fit, and personal benefit of the intervention.

All interviews at t1 and t2 will be recorded and transcribed following data collection and stored for 10 years. During transcription, the ruleset suggested by Dresing and Pehl [59] will be followed. The spoken content is prioritized accordingly, while information on para- and non-verbal events are omitted. The MAXQDA 2020.4 software will be used for qualitative content analysis according to Kuckartz [60] using a combined model of deductive (a priori) and inductive coding (on the text material).

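### Willingness to participate, the closest measure of demand, is assessed only by interviewing relatives who already enrolled, so it carries no information on uptake

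*Protocol article*

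**What the plan says.** The Abstract states that the main objective "is to specify the demand for an early, low-threshold, and low-cost short intervention and to collect feedback" from 20 relatives. The Introduction words the primary aim differently: it "is to develop and assess the feasibility of a preventive psychological short intervention to relatives of patients with Parkinsonism at early stages", and for the intervention "the feasibility will be assessed via acceptability, fit and subjective benefit".

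Table 2 breaks Acceptance into three items: "Willingness of the target group to participate", reasons for participation, and evaluation of the digital format. The interview is the only instrument named for all three. Section 2.4.2 and Table 1 schedule the interview with relatives at t1 (directly after the intervention) and t2 (6 weeks later), and at no other time.

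Section 2.1 describes recruitment. Marburg uses an internal system that "lists patients with Parkinsonism who are generally interested in participating in studies". Cologne uses lists of people who took part in earlier studies. E-mail lists of self-help groups are added to raise numbers. One inclusion criterion for relatives is that they are willing and equipped to use telemedicine. Section 4 then expects the study to reveal whether the target group accepts the offer.

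**The concern.** Demand in a target group depends on how many of those offered the intervention take it up. That requires knowing about the people who said no. The named instrument reaches only people who said yes and had been offered the sessions before being asked. Their accounts can explain why they joined, but not what share of the target group would join.

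The recruitment sources narrow the view further. Two of the three consist of people with a prior interest or history in studies, and the third of people already in touch with self-help groups. The telemedicine criterion removes those who would reject the medium before acceptance of a digital offer is assessed.

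At stake is half of the Abstract's main objective. Sections 3 and 4 present the pilot as preparation for a larger randomised trial, for which the number of relatives to approach per relative enrolled is a basic planning figure. It is hard to recover later if it was not recorded.

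**Working it through.** **Inputs from the article.** Enrolment: 10 dyads per site at 2 sites, so 2 × 10 = 20 relatives, which reproduces the stated total. No power, precision or uptake figure is given, so there is no further number to reproduce.

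**Input that is an assumption.** The number N of eligible relatives approached. The article does not state it, so a range is shown.

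**What the interview can show.** Let m ≤ 20 relatives be interviewed. All m have enrolled, so enrolment among interviewees is m/m = 100% for every N. Willingness to enrol does not vary within this group.

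**What uptake would show.** Uptake = 20/N. The exact (Clopper–Pearson) limits are: lower = 2.5% quantile of Beta(20, N − 20 + 1); upper = 97.5% quantile of Beta(20 + 1, N − 20).

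| N approached (assumed) | Uptake 20/N | Exact 95% CI | Enrolled among those interviewed |
|---|---|---|---|
| 25 | 80% | 59–93% | 100% |
| 40 | 50% | 34–66% | 100% |
| 60 | 33% | 22–47% | 100% |
| 100 | 20% | 13–29% | 100% |
| 200 | 10% | 6–15% | 100% |
| 400 | 5% | 3–8% | 100% |

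Over this range uptake falls from 80% to 5%, while the last column stays fixed. The intervals for N = 25 and N = 100 do not overlap, so even with 20 enrolled an uptake count would separate high demand from low demand.

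**Precision by site.** With 10 enrolled per site, 10 of an assumed 20 approached is 50% (27–73%). Site-level figures are descriptive only.

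**Limit of the interval.** Recruitment stops at a set number enrolled, so N rather than 20 is the random quantity. The binomial interval is the usual approximation here.

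**The case against.** The strongest reply is that the interviews are qualitative. Section 2.4.2 plans content analysis with deductive and inductive coding, and no willingness percentage is announced. Enrolled relatives can still say that the timing was wrong or the need small. The article also condenses a full protocol that may contain a screening log, and Section 3 already concedes that 20 participants cannot support reliable statements about impact.

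Part of this stands. A missing screening log would not be a finding in itself, and the interview suits reasons for participation and evaluation of the format. But the article does not leave this measure open: Table 2 fixes both the item and its instrument, and the instrument cannot inform the item. The caveat in Section 3 concerns effects of the intervention, not demand.

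Three stronger readings are tempting, and the article does not support them.

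- *Feasibility as a whole cannot come out negative.* Willingness is one of three acceptance items, and acceptance is one of three components of intervention feasibility. Evaluation of the digital format, fit, subjective benefit, the 0–5 session ratings (Section 2.4.3), manual adherence and dropout can all be unfavourable. Failure to reach 20 would also be visible.
- *Relatives who leave early vanish from the data.* They may miss the t1 interview. But ratings are collected around each session, Section 2.4.4 plans an analysis of reasons for dropout, and Section 2.4.1 keeps dropouts in the quantitative analysis. The people not covered are those who declined to join.
- *The later trial will go ahead regardless.* Section 4 does say "Based on this, a multicenter randomized, controlled trial will be implemented", but the preceding sentence plans to modify the intervention and the design in the light of the findings. The wording names no outcome that would stop the trial, yet it does not say that results will be ignored.

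**Conclusion.** The point holds for demand and willingness to participate, and for nothing wider. As Table 2 stands, this item is uninformative about uptake: it reads the same at 80% and at 5%. The Abstract's aim "to specify the demand for an early, low-threshold, and low-cost short intervention" and the expectation in Section 4 about acceptance by the target group are therefore not supported by the named instrument. What the study can support is acceptability among relatives who enrolled from these particular lists.

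The conclusion rests on the timing and instrument stated in Tables 1 and 2 and Section 2.4.2, and on no uptake count being named as a measure of acceptance. The uptake percentages illustrate the size of the gap and depend on assumed denominators; the argument does not. The change should be made because it alters what the pilot can conclude, but it does not call the other feasibility measures into question.

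**What to change.** **Preferred.** In Table 2, change the instrument for willingness from the interview to uptake: consented divided by eligible relatives approached, with an exact 95% CI, by site and recruitment source, and with a short reason for each refusal. Four details matter:

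- For self-help e-mail lists, report the number who responded and state that the denominator is unknown.
- Because enrolment is by dyad, record whether the patient or the relative declined.
- Count separately those excluded only because they were unwilling or not equipped to use telemedicine.
- Describe the result as uptake from these lists, since an uptake count does not remove their selection.

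Keep the interview for reasons for participation and evaluation of the format.

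**Alternative.** If approaches cannot be logged, or have already been made without a record, restrict the objective in the Abstract and the statement in Section 4 to acceptability among relatives who enrolled from these lists.

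**Cost.** The preferred change needs a simple log at two sites and a revised line in Table 2; the alternative needs only rewording. The price of the first is a possibly less favourable acceptance figure, with wide intervals by site and source. The price of the second is giving up the claim about demand.
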